## Abstract

**Background:**

Migraine is a recurrent headache disorder that has a still unclear pathophysiology, involving several circuits of both the central and peripheral nervous system. Monoclonal antibodies acting on the calcitonin gene-related (CGRP) pathway (CGRP-MAbs) are the first drugs specifically designed for migraine; those drugs act peripherally on the trigeminal ganglion without entering the blood-brain barrier. Conversely, neuromodulation techniques such as transcranial direct current stimulation (tDCS) act centrally by increasing or decreasing the neuronal firing rate of brain cortical areas. The aim of the study will be to evaluate whether tDCS, in addition to CGRP-MAbs, is an effective add-on treatment in reducing headache frequency, intensity and acute medication use in patients with migraine. To demonstrate the biological effects of tDCS, the electroencephalographic (EEG) power changes after tDCS will be assessed.

**Methods:**

We will include patients with migraine on treatment with CGRP-MAbs and reporting ≥8 monthly migraine days. During a prospective 28-day baseline period, patients will fill in a headache diary and questionnaires to evaluate migraine-related disability, anxiety and depressive symptoms, sleep quality, and health-related quality of life. Subjects will be randomly assigned in a 1:1 ratio to active or sham tDCS. The stimulation protocol will consist in five daily sessions, the cathodes will be applied bilaterally above the occipital areas, with the reference anode electrodes positioned above the primary motor areas. Before the first, and immediately after the last stimulation session, patients will perform a 10-min resting EEG recording. During a 28-day follow-up period following tDCS, patients will have to fill in a headache diary and questionnaires identical to those of the baseline period.

**Discussion:**

This trial will evaluate the efficacy of an add-on treatment acting on the brain in patients with migraine, who are already treated with peripherally acting drugs, showing how tDCS acts in restoring the dysfunctional brain networks typical of the migraine patient.

**Clinical Trial Registration:**

NCT05161871.

## Introduction

Migraine is a recurrent headache disorder representing the second cause of disability under 50 years of age and the first in young women (1). It is a central nervous system disorder whose mechanisms are poorly understood. Electrophysiology (EEG) studies have revealed abnormalities in cortical responsivity to external stimuli, in the different phases of the migraine cycle. During the days between attacks—i.e., the interictal period—, patients with migraine lack of habituation to external stimuli which normalizes in the hours that precede an attack (2). In the premonitory phase of migraine, changes in thalamo-cortical connectivity were observed; the presence of the so-called “thalamocortical dysrhythmia” is supported by MRI studies, before and during migraine attacks (3–5). Those studies showed altered connectivity of the cortex, thalamus, hypothalamus, brainstem and amygdala, which may be involved in the modulation of pain and sensory function (6).

Cortical spreading depression (CSD) is an event occurring in the brain which is supposed to play an important role in the genesis of migraine and to directly generate migraine aura (7). CSD consists in the diffusion of a wave of depolarization in the cerebral cortex that spreads slowly from the posterior areas of the brain; a “second phase” of neurophysiological and vascular changes ensues, characterized by a prolonged direct current potential shift that is lower in amplitude than the initial CSD wave, along with sustained vasoconstriction and reduced blood oxygenation (8). All those events lead to the activation of nociceptive centers, including a peripheral neural structure, the trigeminal ganglion (TG), which releases pain-inducing peptides and mostly calcitonin gene-related peptide (CGRP) (9, 10).

Several drug classes can be used for the prevention of migraine; they can be classified into antidepressants, antiepileptics, antihypertensives, onabotulinumtoxin A, beta-blockers, calcium agonists, and drugs that act on the calcitonin gene-related peptide (CGRP) pathway (11). Preventive drug treatment is not always viable due to potential contraindications; besides, patients may report adverse events or unsatisfactory benefit. Due to non-optimal adherence and poor tolerability to drugs, pharmacological preventive treatment can be replaced or integrated with non-pharmacological methods. Neuromodulation techniques, such as transcranial direct current stimulation (tDCS), are already used as a treatment for migraine and other chronic pain conditions (12–14), and it can be used in patients who prefer non-pharmacological management, or who cannot be adequately managed with drugs.

tDCS is a non-invasive and painless technique of brain modulation, consisting of delivering a weak current (1–2 mA) through two sponge electrodes fixed on the scalp and connected to a battery-driven stimulator; the aim of tDCS is to modulate spontaneous neuronal firing rate by the polarization of resting membrane potential (15). After-effects of the stimulation rely on the modulation of NMDA receptors and synaptic GABAergic activity (15). Anodal stimulation increases cortical excitability by depolarizing neurons in the stimulated area, while cathodal stimulation hyperpolarizes neurons with inhibitory effects (16).

Monoclonal antibodies acting on the CGRP pathway (CGRP-MAbs) are the first preventive drugs specifically designed for migraine; these drugs act by blocking the CGRP pathway, thereby inhibiting vasodilation and the transmission of pain (10). Those drugs demonstrated high efficacy in randomized controlled trials (17–19) and even more effectiveness in real-world studies (20–25). In real-life, the reduction in monthly migraine days due to CGRP-MAbs was up to 12.2 days at 6 months compared with baseline, while monthly days of acute medication consumption decreased up to 8; 50% response rates ranged from 10 to 76.5% (20–26). However, both randomized controlled trials and real-life studies showed that up to one half of patients in clinical practice do not attain a 50% reduction in monthly migraine days from baseline even with those specific treatments and need further improvements in their migraine prevention. Besides, many patients, even if reporting a significant response to those drugs, may have a high number of residual monthly headache days resulting in a substantial impact on daily activities (27). The number of residual monthly migraine days after treatment, although clinically relevant, is not reported by the available studies (28).

Due to their huge molecular dimensions, CGRP-MAbs inhibit CGRP release from the TG without crossing the blood-brain barrier (10); hence, they are not expected to interfere with the mechanisms of migraine occurring within the brain. On the contrary, tDCS acts on the central nervous system, by modulating the electrical activity of areas implied in pain modulation (29). Therefore, tDCS with CGRP-MAbs have different targets located at different levels in the nervous system; hence, we speculate that their combined administration can have a synergistic or additive effect.

## Objectives

The primary aim of the present study will be to assess whether tDCS as an add-on treatment to CGRP-MAbs is effective in reducing headache frequency, intensity, and acute medication use in patients with migraine. Secondarily, we will assess the effect of tDCS add-on on migraine-related disability, quality of life, sleep disturbance, and psychological symptoms. To demonstrate and quantify the biological effects of tDCS, we will assess the electroencephalographic (EEG) power changes after tDCS.

## Ethical Issues

The study was approved by the Ethics Committee for the districts of L'Aquila and Teramo with Protocol Number 272/21. All patients will sign an informed consent to participate in the study.

## Inclusion and Exclusion Criteria

Our trial will follow the guidelines issued by the International Headache Society for neuromodulation in headaches (30). The protocol follows the SPIRIT checklist (31, 32) (Supplementary Material 1). The inclusion criteria will be the following:

- male or female patients, aged between 40 and 70 years, referring to the Headache Center of the University of L'Aquila;- a diagnosis of migraine with or without aura according to the International Classification of Headache Disorders, 3rd Edition (33);- migraine must have been present for at least 12 months;- treated with CGRP-MAbs (erenumab, fremanezumab or galcanezumab) for 90–180 days since the first subcutaneous administration (this time range was chosen to ensure a stable CGRP pathway inhibition);- reporting ≥8 monthly migraine days in the last 30 days of observation despite treatment with CGRP-MAbs;- able to discriminate between migraine and tension-type headaches;- written informed consent to participate in the study.

Treatment with CGRP-MAbs will be prescribed according to Italian reimbursement criteria, i.e., in patients reporting ≥8 monthly migraine days with a Migraine Impact and Disability Assessment Scale score ≥11 and having failed at least three preventive medication classes among beta-blockers, tricyclic antidepressants, anticonvulsants, and onabotulinumtoxinA.

Patients with other concomitant primary headache types will be included if attacks are <1 day/month and <12 days/year.

Subjects with medication overuse headache and menstrually-related migraine will be not excluded from the study but will be included in exploratory subgroup analyses. According to the clinical practice of the recruiting center, patients with medication overuse will not undergo detoxication treatments.

The exclusion criteria will be the following:

- use of any concurrent migraine preventive medication other than CGRP-MAbs;- secondary migraine-like headache;- epilepsy or any other neurologic condition that may be worsened by transcranial electrical stimulation;- metallic head implants, cardiac pacemaker or any other device that could malfunction or be displaced by electrical stimulation;- pregnancy or lactation.

Acute migraine treatment will be allowed during the study. Migraine preventive treatments other than CGRP-MAbs must be withdrawn for at least 60 days before inclusion in the trial.

## Visit Schedule and Assessment

The study includes a 90- to 180-day retrospective screening period, a 28-day baseline period, a 5-day stimulation period, and a 28-day follow-up period. The planned inclusion period of the study will be 12 months. Assessment schedule is summarized in Table 1.

**Table 1 T1:** Assessment schedule.

	**Screening**	**Baseline**	**Stimulation**	**Follow-up**
Informed consent	X			
Inclusion/exclusion criteria	X	X		
Clinical history	X	X		
Demographic data	X	X		
Headache diary	X*	X	X	X
mMIDAS		X		X
HIT-6		X		X
HADS		X		X
SF-36		X		X
PSQI		X		X
EEG		X	X	

*CGRP-MAbs indicates monoclonal antibodies acting on the calcitonin gene-related peptide pathway; EEG, electroencephalogram; HADS, Hospital Anxiety and Assessment Scale; HIT-6, Headache Impact Test-6; mMIDAS, modified Migraine Impact and Disability Assessment Scale; PSQI, Pittsburgh Sleep Quality Index; SF-36, Short Form Health Survey. *Retrospective assessment based upon the Headache Center diary used in clinical practice*.

At the beginning of the study, all subjects will be thoroughly informed about all aspects of the study, including the study treatment, visit schedule, required evaluations, diary compliance, and all regulatory requirements for informed consent. Subjects who sign an informed consent but fail to be assigned to the study treatment for any reason will be considered a screen failure. The reason for not being started on treatment will be recorded.

Subject demographic and baseline characteristic data will be collected on all subjects. This will include age, race, ethnicity, and relevant physiological and medical history. Prior headache characteristics and previous headache medication history, including information on the suitability for migraine prophylactics and prior migraine prophylactic treatment failure history, will be collected as part of screening and baseline characteristics.

## Study Procedures

### Baseline

Eligible subjects will undergo a 28-day baseline period to confirm their eligibility, by filling out a headache diary containing information about headache occurrence, its intensity on a 1–10 Numerical Rating Scale, its duration (in hours), associated symptoms (nausea, vomiting, photophobia, phonophobia), and consumption of drugs for the acute treatment. For each headache day, patients will have to rate their degree of headache-related disability as low-medium, or high (Supplementary Material 2).

At baseline, subjects will have to fill out questionnaires to assess migraine-related disability, quality of life, sleep disturbance and psychological aspects: the modified Migraine Disability Assessment (mMIDAS); the Headache Impact Test-6 (HIT-6); Short Form Health Survey (SF-36); Pittsburgh Sleep Quality Index (PSQI); Hospital Anxiety and Depression Scale (HADS).

### EEG Recording

Patients will perform a 10-min resting EEG recording (5 min eyes-open, 5-min eyes-closed), immediately before the first and immediately after the last tDCS session. EEG will be performed with a 64-channel apparel (BrainAmp, Brain Products GmbH) according to the 10–10 international system.

### Follow-Up

Patients will undergo a 28-day follow-up assessment period starting from the day following the last tDCS session, filling out a diary identical to those of the baseline period. At the end of the follow-up period, patients will fill out the same questionnaires as during the baseline period. To verify blindness, patients will also be asked whether they received active or sham tDCS. The study procedures are summarized in Figure 1.

**Figure 1 F1:**
[figure not shown]
Schematic representation of trial procedures. Mab indicates monoclonal antibody; EEG, electroencephalogram; tDCS, transcranial direct current stimulation. In the transcranial direct current stimulation figure, blue squares indicate the cathodes, while red squares indicate the anodes.

## Study Discontinuation

The study will be discontinued under the following circumstances:

- Subject decision;- Pregnancy;- Failed to meet the inclusion/exclusion criteria at any time during the study;- Any situation in which study participation might result in a safety risk to the subject;- Any change (initiation, withdrawal, or dosing change) in concurrent medication, including preventive and abortive treatment for migraine;- New diagnosis of diseases that may be negatively affected by tDCS, such as epilepsy.

Study subjects will be consecutively recruited until the number of subjects completing the study reaches the number of 30 (15 treated with tDCS and 15 with sham stimulation). In case of screening failure or any of the conditions listed above and leading to study discontinuation, subjects will be replaced, provided that their inclusion falls within the 12-months inclusion period.

Patients discontinuing CGRP-MAbs due to non-response or lack of tolerance, as well as patients starting oral migraine preventive treatments as add-on, will be excluded from the study due to change in their medication. To ensure that treatment with CGRP-MAbs is stable and well-tolerated and to minimize the risk of including patients who will then withdraw treatment with CGRP-MAbs or change their medication, patient screening will be performed after 90–180 days from the first MAb administration. Patients lost to follow-up, unwilling to continue the trial, or developing a contraindication to continue the trial, will be excluded from efficacy analyses; their adverse events will be monitored and reported.

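### Randomised patients are removed and replaced for medication changes, including acute drugs, that can depend on how they respond

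*Protocol article*

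**What the plan says.** All references are to the protocol article.

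- **Study Discontinuation, medication trigger:** "Any change (initiation, withdrawal, or dosing change) in concurrent medication, including preventive and abortive treatment for migraine".
- **Study Discontinuation, eligibility trigger:** "Failed to meet the inclusion/exclusion criteria at any time during the study".
- **Study Discontinuation, replacement:** "In case of screening failure or any of the conditions listed above and leading to study discontinuation, subjects will be replaced", as long as the new subject falls within the 12-month inclusion period. The target counts completers: "Study subjects will be consecutively recruited until the number of subjects completing the study reaches the number of 30", 15 per arm.
- **Study Discontinuation, exclusion:** patients who stop the antibody for non-response or poor tolerance, or who add an oral preventive, "will be excluded from the study due to change in their medication". Those lost, unwilling or newly contraindicated are left out of the efficacy analyses.
- **Inclusion and Exclusion Criteria:** "Acute migraine treatment will be allowed during the study". One criterion is "reporting ≥8 monthly migraine days in the last 30 days of observation despite treatment with CGRP-MAbs".
- **Objectives:** the primary aim is to learn whether add-on tDCS "is effective in reducing headache frequency, intensity, and acute medication use in patients with migraine".
- **Efficacy Outcomes:** the primary outcome is the change in headache days between the two 28-day periods. Changes in migraine days and in acute doses are secondary outcomes.

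**The concern.** Randomisation makes the arms comparable only if leaving the comparison does not depend on what happens after allocation. Here a change in migraine medication leads to removal and replacement. A patient who is doing badly may switch acute drug, add a preventive or give up the antibody. A patient who is doing well may drop an acute drug. If tDCS works, these events will not be equally common in the two arms, so the completers will have been selected partly on the result.

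Replacement restores the head count but not the comparability. Once participation ends, the diary data may also never be collected, and no later analysis plan can recover them. At stake are the primary headache-day comparison and, more directly, the comparison of acute drug use.

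**Working it through.** **1. Is the rule confined to the time before randomisation?** No sentence in Study Discontinuation says so. The section speaks of stopping the study, of excluding patients who change medication, and of counting completers after stimulation and follow-up. The rule therefore reaches randomised patients.

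**2. What does a change in dosing of abortive treatment mean?** Two readings fit the text.

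- *Broad:* any change in how much acute drug is taken. This would collide with acute treatment being permitted and with acute doses being an outcome.
- *Narrow:* a changed drug or prescribed regimen. As-needed use of an unchanged drug is then compatible with all the sections.

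The article does not choose between them.

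**3. Does the narrow reading remove the problem?** No. A switch of acute drug, an added preventive and withdrawal of the antibody for non-response can all depend on how the patient is doing. For the last of these the article names non-response as a reason.

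**4. The plan's own sample size reproduces.** Inputs from Sample Size: mean changes −4 and −1, SD 2, two-sided 5%, power 80%. The standardised difference is d = 3/2 = 1.5. For a two-sample t-test with n per arm, df = 2n − 2 and the noncentrality is d·√(n/2).

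| n per arm | noncentrality | power |
|---|---|---|
| 8 | 3.00 | 79.7% |
| 9 | 3.18 | 84.8% |
| 15 | 4.11 | 97.7% |

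So 9 per arm is right on the stated inputs. The 15 per arm is described as an allowance for dropouts.

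**5. Illustration of the mechanism (not an estimate).** Take individual changes as normal with the planned means and SD. *Assume* that a share q of the patients whose days increase change their medication and are removed; the article gives no such rate. The probability of an increase is Φ(−4/2) = Φ(−2) = 0.023 in the active arm and Φ(−1/2) = Φ(−0.5) = 0.309 in the sham arm. The share removed is q times that.

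| q (assumed) | removed, active | removed, sham | completer difference (true −3.0) |
|---|---|---|---|
| 0.25 | 0.6% | 7.7% | −2.84 |
| 0.50 | 1.1% | 15.4% | −2.64 |
| 1.00 | 2.3% | 30.9% | −2.09 |

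Check of the last row. Active completers: −4 − 2·φ(2)/Φ(2) = −4 − 2(0.0540/0.9772) = −4.11. Sham completers: −1 − 2·φ(0.5)/Φ(0.5) = −1 − 2(0.3521/0.6915) = −2.02. Difference: −4.11 + 2.02 = −2.09.

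**6. The direction is not fixed.** If the same removal occurred in the active arm only, the difference would be −4.11 − (−1.00) = −3.11, larger than the truth. Which pattern would occur cannot be read from the article.

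**The case against.** **The medication rule is about prescriptions, so nothing contradicts.** This stands in part. A reader might infer that a patient who simply needs fewer doses is expelled and that the sections contradict each other. The text does not establish that, because the narrow reading is available. It is an ambiguity to resolve, and the narrow reading still leaves outcome-dependent removal.

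**Eligibility is a matter for screening and baseline.** This largely stands. A reader might infer from "Failed to meet the inclusion/exclusion criteria at any time during the study" that anyone who falls below 8 migraine days in follow-up is removed as a treatment success. Read literally, the words cover that case. However, Table 1 schedules the eligibility check only at screening and baseline, and the Baseline section uses the 28 days to confirm eligibility. The phrase may equally refer to ineligibility discovered late or to a new exclusion such as pregnancy. The wording is loose, but it does not show that responders will be expelled. Simulating that reading would not settle it: under assumed baseline means from 16.5 down to 10.4 days, the share removed from the active arm runs from 19% to 74%, which mainly reflects the assumption.

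**The antibody window.** A reader might also infer that patients who pass 180 days on the antibody during the study become ineligible. Study Discontinuation ties the 90 to 180 days to screening, so this does not follow.

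**The analysis plan may handle it.** How the analysis treats these patients could be refined there. The rules that stop participation and replace the subject are stated in the article itself, and they decide which data exist.

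**Conclusion.** The point holds for the medication rule. As written, patients may be removed and replaced after randomisation for changes in preventive or abortive treatment, and for abandoning the antibody for non-response. These events can depend on response, so the 15 completers per arm are not a randomised comparison. The eligibility phrase is a secondary matter of loose wording.

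The size and direction of the bias cannot be computed from the article, because it gives neither the rate of medication changes nor their relation to outcome. The shift from −3.0 to between −2.84 and −2.09 days shown above rests on assumed trigger rates and one pattern of removal; another pattern enlarges the difference. A reader should not infer that the effect will be understated, or that responders will be lost mainly from the active arm. The planned sample size is not in dispute.

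**What to change.** **Reconcile the text.** Objectives, Inclusion and Exclusion Criteria, Table 1, Baseline, Study Discontinuation and Efficacy Outcomes should agree on two things: what counts as a medication change, in particular whether as-needed use of an unchanged acute drug does, and at what time eligibility is judged. Which changes should end stimulation or participation is a clinical decision for the sponsor and is not proposed here.

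**Change the analysis set and the replacement rule.**

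1. Keep every randomised patient in the primary efficacy set, in the assigned arm.
2. Continue the diary to day 28 of follow-up after a medication change or discontinuation, where the patient agrees.
3. Record medication changes, with dates, as intercurrent events.
4. Do not replace randomised patients; replace only those who fail before randomisation.
5. Report completers without a medication change as a sensitivity analysis.

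**Cost.** This is more than rewording. The target of 30 completers becomes 30 randomised, which fits Sample Size, where 30 already includes the dropout allowance. At 15 per arm, 15 − 9 = 6 patients per arm could still lack outcome data before the stated minimum of 9 is reached. Diaries must be kept for some patients who have stopped. The primary estimate will include some patients whose medication changed, so it describes the effect of being assigned to tDCS whether or not medication changed; the sensitivity analysis shows the result without them.
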